Therefore, we designed this randomized controlled neuroimaging trial aiming to (1) compare the therapeutic effects of acupuncture and moxibustion alone treating for PDM so as to investigate their respective advantages, (2) investigate the potential central mechanism of acupuncture and moxibustion for PDM using functional magnetic resonance imaging (fMRI), and (3) explore the potential correlations between cerebral activity changes and the improvement of clinical variables elicited by acupuncture or moxibustion.

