### Sample size

According to the statistical requirements of neuroimaging studies, 12–15 individuals in each group is the reasonable sample size for stable cerebral responses [22, 23]. Considering a drop-out rate of 20% and possible excessive head motion during scanning, a sample size of 24 in each group is required, and a total of 72 PDM patients will be recruited.

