### Randomization and blinding

Randomization will be implemented using computer-generated randomization digital table which is created by Excel’s rand function. Seventy-two eligible PDM patients will be randomly assigned to the acupuncture group, moxibustion group, and waiting list group (1:1:1 ratio). Random information will be put into an opaque, sealed envelope and saved by those who will not participate in the study. Due to the particularity operation of acupuncture and moxibustion, it is difficult to blind operators and patients. However, outcome assessors and statisticians were blinded to the procedure and the result of randomization, group allocation, and intervention to reduce the risk of bias.

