### Clinical data analysis

The Kolmogorov-Smirnov test will be used to test the normal distribution of continuous variables. Continuous variables on normal distribution will be presented by mean ± standard deviation, while continuous variables of skewed distribution were expressed as medians and interquartile ranges (IQRs). Analyses will be performed on an intention-to-treat basis. Multiple imputations will be used to handle the missing data. Paired samples *t*-test will be used to compare the clinical outcomes between baseline and end of treatment in each group. Since there are three groups (acupuncture group, moxibustion group, and waiting-list group) with two time points (pre-treatment and post-treatment), the repeated measures analysis of variance (ANOVA) will be employed to analyze the clinical data. In the 2 × 3 group factorial design, the dependent variables were the clinical data collected from pre-treatment and post-treatment, and data in the three different groups will serve as the independent variable. ANOVA and chi-square test will be used to compare group differences at baseline. ANOVA with Šidák corrections will be used to compare the differences between the groups. Clinical data on skewed distribution will be compared using a non-parametric test. A two-sided test is applied for available data, and a *P* value of less than 0.05 is considered statistically significant. Missing data will be replaced by the data from the latest assessment.

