### Neuroimaging data processing and analysis

The fMRI data will be preprocessed and post hoc analyzed by the SPM12 software (http://www.fil.ion.ucl.ac.uk/spm/) and CONN toolbox (http://www.nitrc.org/projects/conn) performed on MATLAB 2015b (MathWorks, Inc., Natick, MA, USA). The preprocessing steps will include slice timing correction, head motion correction, spatial normalization, spatial smoothing, and detrending. After data preprocessing, amplitude of low-frequency fluctuation, regional homogeneity, and functional connectivity will be used to investigate the cerebral responses of the different study groups. ANOVA will be used to evaluate possible cerebral responses in each group by within-group analysis (post-treatment minus pre-treatment). A threshold of voxel-wise *P* < 0.005 uncorrected and cluster-level *P* < 0.05 false discovery rate (FDR) corrected will be applied to all analyses. Pearson’s correlation test will be conducted to investigate the changes between fMRI data and corresponding clinical data in each group.

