## Discussion

“If acupuncture cannot achieve the purpose of treatment, moxibustion is more appropriate” is a classic exposition on the rational clinical application of acupuncture therapy and moxibustion therapy. This study is the first to investigate the central mechanism of acupuncture therapy and moxibustion therapy for patients with PDM. The results will deepen the understanding of the similarities and differences between acupuncture and moxibustion in clinical efficacy and their central mechanism.

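### The brain-symptom correlation is tested arm by arm with no comparison between arms, so it cannot show that acupuncture and moxibustion differ in this link

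*Protocol article*

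**What the plan says.** The third aim, at the end of the Background, is to "explore the potential correlations between cerebral activity changes and the improvement of clinical variables elicited by acupuncture or moxibustion". The method is given in the last sentence of Neuroimaging data processing and analysis: a Pearson "correlation test will be conducted to investigate the changes between fMRI data and corresponding clinical data in each group". The article describes no test of one arm's coefficient against another's, and no model that takes the arms together for this question.

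The closing paragraph of the Discussion section on methodological quality control says that differences between the two therapies in efficacy and central mechanism will be studied in two ways. One compares symptom improvement and cerebral responses across the three groups. The other is the correlation of cerebral change with clinical improvement. The opening of the Discussion expects the results to inform on "similarities and differences between acupuncture and moxibustion in clinical efficacy and their central mechanism".

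Under Sample size, the basis is that "12–15 individuals in each group is the reasonable sample size for stable cerebral responses". "Considering a drop-out rate of 20% and possible excessive head motion during scanning", the article concludes that "a sample size of 24 in each group is required". It gives no size of correlation and no power for the correlation analysis. Clinical data analysis sets two-sided testing, where a P "value of less than 0.05 is considered statistically significant".

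**The concern.** A correlation tested within one arm says whether the association is distinguishable from zero in that arm. It does not say whether the association differs between arms. Yet the article presents the correlation as one of its routes to a difference between the therapies. If nothing compares the coefficients, the informal substitute is to note which arms reached significance. With about 20 patients per arm, chance alone will often split two arms that share the same true association.

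An association common to both therapies could then be reported as a mechanism specific to one of them. The converse matters too: two significant arms, or two non-significant ones, do not establish that the mechanisms are similar.

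**Working it through.** **Inputs from the protocol article.** 24 per arm and 20% drop-out (Sample size); two-sided 5% (Clinical data analysis); correlation run in each group (Neuroimaging data processing and analysis).

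**The plan's own figure.** Starting from 15 per group, 15/0.8 = 18.75, or 19. Reaching 24 needs a further loss of about 20% for head motion: 15/(0.8 × 0.8) = 23.4, or 24. The article does not quantify that loss, so 24 can be neither reproduced nor refuted. In the other direction, 24 × 0.8 = 19.2, so about 19 per arm remain before head-motion exclusions. I use 19 and 24 as the range.

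**Assumption.** The article gives no expected correlation, so I show a range of true r, taken as equal in the two active arms, with bivariate normal data and independent arms.

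**Power per arm.** With Fisher's z the standard error is 1/√(n−3): 0.250 at n=19 and 0.218 at n=24. The r detectable with 80% power is tanh((1.96+0.84)/√(n−3)), which is 0.60 at n=19 and 0.55 at n=24. At r=0.4, atanh(0.4) = 0.424. Then 0.424/0.250 − 1.96 = −0.27 gives 40% power, and 0.424/0.218 − 1.96 = −0.02 gives 49%. Simulation of the Pearson t-test (200,000 replicates) gives 41% and 51%, and the table uses the simulated values.

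**Chance of a split.** If each arm has power p, exactly one of the two is significant with probability 2p(1−p). At r=0.4 and n=19, this is 2 × 0.41 × 0.59 = 0.48.

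| True r in both arms | Power per arm, n=19 / n=24 | One significant, one not, n=19 / n=24 |
|---|---|---|
| 0.2 | 13% / 15% | 23% / 26% |
| 0.3 | 24% / 30% | 37% / 42% |
| 0.4 | 41% / 51% | 48% / 50% |
| 0.5 | 61% / 73% | 47% / 40% |
| 0.6 | 81% / 90% | 30% / 18% |
| 0.7 | 95% / 98% | 10% / 4% |

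The expression 2p(1−p) cannot exceed 50%, and reaches it only when power is 50%. If head motion left 15 in an arm, power at r=0.3, 0.4, 0.5 and 0.6 would be 19%, 33%, 50% and 70%.

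**Example at n=24 per arm.** For r=0.5, t = 0.5 × √22/√0.75 = 2.71, P=0.013. For r=0.3, t = 0.3 × √22/√0.91 = 1.47, P=0.15. Tested against each other, z = (0.549 − 0.310)/√(2/21) = 0.777, P=0.44. One arm is significant and the other is not, with no evidence that they differ.

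**What a direct comparison achieves.** When the true correlations are equal, it declares a difference 5% of the time. For r=0.5 versus 0, z is 0.549/√(2/16) = 1.55 at n=19 and 0.549/√(2/21) = 1.78 at n=24, giving power of 34% and 43%. For 80% power the contrast must be about 0.76 versus 0 (n=19) or 0.70 versus 0 (n=24). These are Fisher z figures; they approximate the interaction test when the spread of brain and symptom change is similar across arms.

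**Pooling the two active arms.** The within-arm correlation pooled over acupuncture and moxibustion has standard error 1/√(2(n−3)). At r=0.4, 0.424 × √32 − 1.96 = 0.44 gives 67%, and 0.424 × √42 − 1.96 = 0.79 gives 78%. The matching Fisher z figures for one arm are 40% and 49% (41% and 51% simulated).

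**The case against.** The aim is worded as exploration, and a correlation within each arm is a legitimate descriptive answer to it. The article says that a detailed analysis plan exists, and a comparison of coefficients may be in it. The article also nowhere says that a significant result in one arm and a non-significant one in the other will be read as a difference. All of this is fair and limits the weight of the point. It does not remove it, because the article fixes both the test and its unit of analysis, and gives that test a role in contrasting the therapies which it cannot fill.

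A reader might infer that separate significance verdicts are the only route left to a difference in central mechanism. The documents do not support that: cerebral responses are separately compared across the groups. The gap concerns the brain-symptom link alone.

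A reader might also want to pool all three arms, which at r=0.4 would give about 84-92% power (0.424 × √48 − 1.96 = 0.97; 0.424 × √63 − 1.96 = 1.40). That requires untreated patients to share the same correlation, whereas the third aim concerns associations elicited by the two treatments. The comparable gain is the 67-78% from the active arms.

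Finally, the remedy is itself weak at this sample size. That stands, and belongs in the report. It is a reason for caution about any claim of difference, not for comparing P values between arms.

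**Conclusion.** The point holds as a minor-to-moderate one. As described, the correlation analysis cannot support a statement that acupuncture and moxibustion differ, or agree, in how brain change relates to symptom change. Each arm's test has less than 80% power unless the true r is about 0.55 (n=24) to 0.60 (n=19).

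It is tempting to say that two arms with the same association will disagree about half the time. The protocol does not support that as a general statement. Half is the mathematical ceiling, and the rate is 40-50% only if the true r is about 0.4-0.5, a value the article does not give; outside that range it falls as the table shows. Disagreement here means significant versus not significant, not opposite signs.

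The figures assume two-sided 5% and 19 to 24 usable patients per arm. Head-motion losses would lower power further. So would applying the stricter imaging threshold to the correlations: at an illustrative 0.5% level, power at r=0.5 is 27% (n=19) to 39% (n=24).

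**What to change.** For each brain measure, fit one regression of symptom change on brain change, arm and arm-by-brain-change over the scanned patients. Report the arm-specific slopes with confidence intervals. Claim an acupuncture-moxibustion difference in this link only from the interaction contrast between those two arms. Keep the per-arm Pearson correlations as description, and state that a significant/non-significant split will not be interpreted as a difference.

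If a common slope is wanted, estimate it from the two active arms only, adjusted for arm, and show the waiting list separately.

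The cost is a change of analysis wording, with no new data. There are two downsides to state. The interaction contrast has low power, so a non-significant result must not be reported as similarity; the interval should carry the message. The common slope assumes similar slopes in the two active arms, which the interaction can check only weakly.

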## Discussion

“If acupuncture cannot achieve the purpose of treatment, moxibustion is more appropriate” is a classic exposition on the rational clinical application of acupuncture therapy and moxibustion therapy. This study is the first to investigate the central mechanism of acupuncture therapy and moxibustion therapy for patients with PDM. The results will deepen the understanding of the similarities and differences between acupuncture and moxibustion in clinical efficacy and their central mechanism.

### Rs-fMRI is an appropriate approach to explore the central mechanism of acupuncture and moxibustion

Since the mid-1990s, quantifying how acupuncture and moxibustion affect the activity of the central nervous system (CNS) with neuroimaging techniques has attracted increasing attention. With the advantages of non-invasive, non-radiation, and high temporal and spatial resolution, fMRI has emerged as the most widely used neuroimaging technique [33–35]. Our previous bibliometric study also demonstrated that 82.14% of the acupuncture-neuroimaging studies used fMRI to explore the cerebral responses to acupuncture stimulation [36]. Resting-state (rs)-fMRI, one of the main types of fMRI, refers to the spontaneous regulation activity of neurons in the relevant brain area of the brain obtained by MRI when subjects are awake and in the resting state without specific brain activity [37]. Compared with task-related fMRI, rs-fMRI helps to better elucidate the intrinsic and spontaneous neural activity of the brain. In recent years, a large number of rs-fMRI studies have been performed to unravel the mystery of brain regulation of acupuncture analgesia [38–40]. Taken together, rs-fMRI can be a useful tool to investigate the central mechanism of acupuncture and moxibustion.

### Central mechanism plays an important role in achieving the efficacy of both acupuncture and moxibustion

Accumulating evidences suggest that the response and integration of the central system to acupuncture stimulation are an important factor affecting the acupuncture effect [17]. The therapeutic effects of acupuncture depend on its dynamic reconfiguration of complex neural networks [41]. Our previous rs-fMRI study demonstrated that acupuncture could achieve treatment effects by modulating brain networks associated with the descending pain modulatory system in patients with PDM [42].

At the same time, neuroimaging studies on moxibustion have also gradually aroused the investigator’s interest. For example, the study has shown that the use of moxibustion can relieve pain via correcting abnormal brain changes in patients with visceral pain [18]. It suggested that information integration of moxibustion stimulation in the central system is the key link to achieve the effect of moxibustion. In addition, Bao et al. [19] compared the brain responses of acupuncture and moxibustion in Crohn’s disease and found that acupuncture regulated the homeostatic afferent processing network, while moxibustion mainly regulated the default mode network of the brain. These studies provide references and the possibility to explore the difference between acupuncture and moxibustion from the perspective of the central mechanism.

### Methodological quality control is crucial to ensure the repeatability of the results

Strict quality control is essential to improve the reliability of the study and should be used throughout the test. In this trial, quality control will be strengthened in three aspects. Firstly, when recruiting patients, we establish rigorous inclusion and exclusion criteria. In addition to demographic characteristics, other factors such as the usage of medication that may influence cerebral activities are also considered. Because PDM is often accompanied with anxiety and depression, SAS and SDS are used to assess the emotional state. Secondly, in order to ensure the curative effect, unified training will be conducted before the acupuncture and moxibustion operation. After the training is qualified, the two acupuncturists will follow the strict and standard operating procedures. Thirdly, baseline data will be collected on the first day of the menstrual cycle. Participants will be asked to maintain their regular lifestyle and avoid staying up late and ingesting alcohol and caffeine 24 h before the scan. Meanwhile, participants will be asked to follow uniform instructions, wear earplugs, close their eyes, and remain relaxed and awake during the scan.

Acupuncture and moxibustion are effective interventions in PDM treatment, but their central mechanism remains unclear. This trial is designed to investigate the differences between acupuncture and moxibustion in clinical efficacy and central mechanism through the following two aspects. On the one hand, the symptom improvement and cerebral responses to acupuncture, moxibustion, and waiting list will be compared, and on the other hand, the correlation between the cerebral activity changes and clinical variables’ improvement will also be analyzed.

### The strengths and limitations of this study

There are some strengths of this study as follows. Firstly, acupuncture and moxibustion, as two important parts of the external treatment of TCM, are widely used to treat various pain diseases, including PDM. Although previous studies have found that acupuncture and moxibustion can effectively relieve the clinical symptoms of patients with PDM [12, 13, 15], the difference in clinical efficacy and the underlying mechanism remains unclear. Therefore, this study will first investigate the potential similarities and differences between acupuncture and moxibustion in clinical efficacy and central mechanism for patients with PDM. Secondly, this study will observe structural and functional changes in the patients with PDM at baseline and at the end of the treatment. The application of a randomized controlled neuroimaging trial will provide objective and valid evidence on how acupuncture and moxibustion treatment relieves dysmenorrhea by modulating brain networks associated with pain and analgesia.

There are also some limitations in this study. Firstly, due to the particularity of acupuncture and moxibustion operation, the blind method cannot be achieved. Secondly, this study focused on the clinical symptoms and structural and functional changes in the patients with PDM before and after acupuncture or moxibustion treatment, so the follow-up period of patients is not investigated in this study.

### Trial status

This trial was registered at the Chinese Clinical Trial Registry (http://www.chictr.org.cn) on 27 February 2021 (registered number: ChiCTR2100043732, the protocol version number: V2.0). This study is currently in the recruitment stage. The first patient was enrolled on 1 March 2021. Recruitment will be approximately completed before 30 June 2022, and the trial is estimated to end in December 2022.

## Data Availability

The data and the relevant results in this study will be shared through scientific papers.

## Abbreviations

AE: Adverse events
ANOVA: Analysis of variance
BOLD-fMRI: Blood oxygenation level-dependent functional magnetic resonance imaging
CDUTCM: Chengdu University of Traditional Chinese Medicine
CMSS: COX menstrual symptom scale
CNS: Central nervous system
CRF: Case report form
3D-T1WI: Three-dimensional T1-weighted imaging
FDR: False discovery rate
fMRI: Functional magnetic resonance imaging
FOV: Field of view
NSAIDs: Nonsteroidal anti-inflammatory drugs
PCS: Pain catastrophizing scale
PDM: Primary dysmenorrhea
QoL: Quality of life
SAE: Serious adverse events
SAS: Self-rating anxiety scale
SDS: Self-rating depression scale
SF-36: 36-Item short form health Survey
TCM: Traditional Chinese medicine
TE: Echo time
TR: Repetition time
VAS: Visual analog scale
